#### Demographic characteristics

The initial assessment information will include age, gender, height, weight, educational level and job information related to low back pain (pain location, duration, use of medication and previous treatments).

#### STarT Back Screening Tool

The SBST-Brazil questionnaire is a prognostic evaluation tool which aims to classify patients into low, medium or high risk of developing long-term pain or disability related to psychosocial factors [30, 31]. The questionnaire contains questions related to pain, disability, comorbidities, bothersomeness, pain catastrophizing, fear, anxiety and depression. For scoring and classification, the patient must choose between “agree” (1 point) or “disagree” (0 points) on the first eight questions. Question 9 contains five possible answers: not at all (0 points), slightly (0 points), moderately (0 point), very much (1 point) and extremely (1 point). The total score of the SBST-Brazil represents the sum of all questions and ranges from 0 to 9. Scores ≤3 points classify the patient as low risk. Scores ≥4 points indicate the need to examine the psychological subscale comprised of questions 5 to 9. Patients with scores ≤3 points on the psychological subscale are classified as medium risk and patients with scores ≥4 are classified as high risk. The SBST-Brazil was only used for screening and not as an outcome measure instrument.

#### Pain Numerical Rating Scale

The Pain Numerical Rating Scale is a scale of 11 points (0–10) that aims to measure the intensity of pain reported by the patient, where 0 = “no pain” and 10 = “pain as bad as could be” [32]. In this study patients will be asked about their pain intensity in the last 7 days.

#### Patient-Specific Functional Scale

The Patient-specific Functional Scale provides reliable measurements of limitations in specific tasks [32]. The patient is asked to choose three activities that they cannot perform or can perform with difficulty because of pain. Each activity is scored on a Likert scale that ranges from 0 (unable to perform the activity) to 10 (able to perform the activity at preinjury level). The final result is the average of the three scores from 0 to 10 points. High values indicate a lower degree of limitation in performing specific tasks [33, 34]. This questionnaire presents good responsiveness with patients with low functional limitation [16].

#### Oswestry Disability Index

The Oswestry Disability Index aims to assess disability associated with low back pain [35, 36]. This questionnaire consists of 10 items describing everyday situations that patients may find difficult to perform due to low back pain. Each of the 10 items is scored from 0 to 5, adding up to a maximum score of 50 points. The result is multiplied by 2 to obtain a percentage. From this obtained percentage it is possible to classify the patients as having: minimal disability (0% to 20%), moderate disability (20% to 40%), severe disability (40% to 60%), crippled (60% to 80%) and bedridden (80% to 100%).

#### Global Perceived Effect Scale

The Global Perceived Effect Scale seeks to evaluate clinical changes perceived by the patient by comparing the onset of symptoms to the current situation [32]. It is an 11-point grading scale (−5 to 5) wherein −5 = vastly worse; 0 = no change; and 5 = completely recovered. High scores indicate greater perceived recovery of the condition [32]. This scale is more responsive with patients who have low functional limitation [16].

#### Consultation and Relational Empathy – CARE

The Consultation and Relational Empathy (CARE) Measure is a questionnaire to assess patients’ perception of empathy and communication during consultation [37–39]. It consists of 10 questions answered according to a Likert scale of 1 to 5 (where 1 = poor and 5 = excellent). The final score is obtained by adding the questions’ scores, with a maximum score of 50 and a minimum score of 10 points. High values indicate greater empathy. Each question contains a “not applicable” answer; in this case, the item must be excluded and the result will be obtained from the average score of the questions answered [37]. The questionnaire will be applied by a blinded assessor after the first treatment session.

#### Expectation and credibility

Improvement expectation will be assessed by a numerical scale of 11 points, with 0 = “no expectation of improvement” and 10 = “the highest expectation of improvement” [40]. Credibility regarding the treatment will be evaluated by four questions. These questions include confidence-related issues that treatment can help to ease and deal with pain, confidence in recommending treatment to other patient and how much treatment makes sense to the patient. These questions will be scored according to a Likert scale ranging from 0 (no confident) to 6 (totally confident) [40]. Expectation and credibility will be evaluated after a week of randomization.

### Treatment protocol

Patients will be randomized into three groups: a Positive Therapeutic Alliance (PTA) group, a Usual Treatment (UT) group and a Control group (CG). Treatment sessions will be conducted face-to-face and individually with each patient. The treatment sessions will be delivered by two physical therapists with postgraduate qualifications and a completed Master’s degree in the research field.

The treatment protocol offered to the PTA and UT groups will be based on research that demonstrates the effectiveness of empathy and communication training with patients [26–28, 41]. Patients in the PTA and UT groups will receive two 60-min treatment sessions with a 1-week interval. The sessions will be held in an ordinary physical therapy office following the standards of comfort, organization and hygiene. The treatment protocol is initially structured in education and differentiation regarding the nonverbal behavior of the therapist and key issues related to the treatment. In order to ensure treatment fidelity, and to standardize the information that will be provided to patients in both groups, the therapists will follow a description of the relevant issues to be addressed during treatment (Tables 2 and 3). The treatment protocol recommendations were developed based on previous studies and designed to ensure the enhancement of the therapeutic alliance in one group and reduce it in the other [26–28, 41]. Considering the type of intervention, the therapists will not need any physical or informational materials to deliver the intervention. It is important to emphasize that the PTA and UT groups will receive the same informational content related to low back pain. The difference will be the form used to transmit this information.

**Table 2 Tab2:** Topics to be addressed during therapy in Positive Therapeutic Alliance and Usual Treatment Groups [9, 27, 41–43, 47–54]

Addressed topic	Key issues to be discussed	Example sentences
Regarding low back pain	• Low back pain causes • Low back pain diagnosis • Low back pain classification • Prognosis • Low back pain natural history	“Permanent or severe back damages are rare” “It is really very difficult to damage your back” “Back pain is rarely caused by a serious illness” “Back pain prognosis is favorable”
Imaging tests	• Imaging findings in asymptomatic people • Normal degenerative signs	“About 60% of the asymptomatic population has some sort of degenerative sign” “There is nothing seriously wrong in your back”
Physical activity and Rest	• The importance of physical activity • Low back pain behavior	“The sooner you resume your activities the sooner you will get better” “Rest is not good for the back” “You may have some limitations, but the most important thing is to keep moving”
Pain control	• Medication • Available treatments • Self-care	“There are several steps you can take to help your back pain” “Physicians and physical therapists can help your back pain, but only you are able to take care of yourself”
Family and work, anxiety and stress-related factors	• The importance of family support • The importance of controlling anxiety and stress • The influence of these factors on back pain	“Gradually return to your social activities and work! The sooner you return, the less future problems you will have” “You really can help yourself!” “People who cope better with the pain return to their activities faster and better” “You will have good and bad days, this is normal!” “Although the natural history is positive, there are some factors that contribute to pain that becomes chronic, we will work on them”
Concepts of chronic pain	• Current concept of pain • Pain threshold • Central hypersensitivity	“Pain does not mean back injury” “Pain is a response to sensory stimuli, and it is not necessarily related to any tissue damage in the spine” “Pain can just be a misunderstanding of the body”
Encouragement ^51,55^	• Good prognosis: subgroup of low risk of involvement of psychosocial factors • Return to activities	“This information is taken from the best and most current research in the world” “Do not let your back pain take over your life, you are able to get through it”

**Table 3 Tab3:** Guidelines for standard treatment sessions of the Positive Therapeutic Alliance Group [55–59]

Addressed aspect	Description	Key issues to approach
Appointment outset	A warming and caring reception	“Hello! I was waiting for you!” “Apart from the pain, are you all right today?”
Demographic questions	Show interest in getting to know the patient	“I think I know your family name…” “Tell me more about yourself”
Medical diagnosis	Ask about patient’s condition in an interested manner	“This part of the assessment interests me very much, tell me about your condition, what did the physician say?”
Primary complaint	Demonstrate interest in the current complaint	“In your daily routine, what bothers you the most? What is your primary complaint? Tell me so I can help you.”
Clinical history	Address issues about the patient’s condition (beginning, development, current condition) Inquire about medical history, involving other issues, not only low back pain	“First, I have a few questions that will help me better understand your pain”
Pain location	Investigate and demonstrate an effort to understand the patient’s pain complaint	“Use your hand to show me where your pain is” “From this point, does this pain go up/down or sideways?
Pain behavior	Investigate and demonstrate an effort to understand the patient’s pain complaint	“I am also interested in your personal symptoms” “Does this pain change during the day?” “Describe the pain to me” “Which activity of your daily life makes the pain worse?”
Primary limited daily activity	Question the patient demonstrating an interest in a way to encourage a return to activities	“How did this pain affect your lifestyle?”
Session closure	Reinforce positive messages	“You did very well today! And certainly you will be fine” “I understand that these chronic situations sometimes get out of our control, but I am sure you will do well” “No matter what happens. Try to be patient with yourself and look for positive things that are happening to you ”
Eye contact	Maintain eye contact while listening to the patient	-
Facial expressions in response to patients’ questions	Demonstrate emotions through facial expression Facilitate nonverbal communication through facial clues	-
Posture	Adopt a posture of attention, mutual respect and receptivity	-
Tone of voice	Use different tones of voice to emphasize the importance or the focus on a particular subject during treatment	-
Affection	Demonstrate the importance of patient participation in the therapeutic process Ask about emotional aspects	-
Understand the biopsychosocial context	Address issues related to work, family and social life	-
Shared decision making	Share decision-making regarding treatment Involve the patient in the healing context	“Shall we set some goals together in order to improve your condition?”
Demonstration of empathy	Reflect the emotions that patients present Create an environment of comfort and responsiveness	“Your back pain must be very hard for you” “I can put myself in your shoes and feel how that pain hinders you”
Concerning the treatment provided	Focus on information about the success of treatment, based on the best available scientific evidence	“The treatment being offered to you is scientifically proven to be the most suitable for your case”
Personal experience	Demonstrate successful experiences with similar cases	“The clinical experience I have had with this new treatment is promising! Often patients already feel much better soon after the treatment”

The patients in the PTA group will undergo an intervention based on treatment guidelines involving guidance and information related to a return to daily activities, advice on dealing with the pain and clear explanation of their signs and symptoms [9, 18, 42, 43]. The sessions will be structured with the intention of increasing therapeutic alliance and empathy, based on topics relating to the condition and behavior taken from *The Back Book* [43]. UT-group patients will also receive the same informational content on low back pain based on *The Back Book* [43]. Therapy sessions will be performed with limited interaction between patient and therapist and the information will be transmitted in a clear and straightforward manner [23]. Patients in the CG will not receive any treatment and will be instructed not to seek treatment for the first month after randomization. The treatment offered to the PTA or UT groups will be available for patients who are interested after a period of 1 year. Patients will not be limited in looking for other types of treatment after the first month and will be evaluated at baseline and during every reassessment. Since patients will be recruited from a waiting list and will receive the care offered in this study after 1 year, we believe that this conduct does not violate any ethical principles with these patients.

Patients who require additional interventions other than those offered by this study will be referred for treatment at teaching clinics of the participating universities. Patients’ use of medication will not be limited and will be controlled at each reassessment. Patients will be advised not to seek other treatment options during the intervention period. Patients will not receive any financial compensation for participation.

### Statistical analysis

A researcher not involved in data collection and without any conflict of interest will be responsible for monitoring data. The randomization process and blinding of patients and assessors will be audited monthly by an experienced researcher. All data will be entered twice before statistical procedures. A researcher who will receive the data in an encrypted format to ensure confidentiality will conduct the statistical analysis.

Linear mixed models will be used for primary analysis to verify the differences between the average effects of interventions in reassessments carried out 1 month, 6 months and 12 months after randomization. The differences between groups will be calculated by interaction terms of groups versus time. The time will be coded as a categorical variable (baseline, 1 month, 6 months and 12 months after randomization). No interim analysis will be performed. The process of analysis of treatment efficacy will follow the intention-to-treat analysis [44]. If a patient abandons treatment or refuses to answer any reassessment, the lost data will not be replaced. All statistical procedures will be performed with a significance level of 5% and through the SPSS 19 software for Windows.

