### Sample size calculation

The sample size calculation was carried out to detect a difference of 1 point on the Pain Numerical Rating Scale (estimated standard deviation = 1.84) and 1 point on the Patient-specific Functional Scale (estimated standard deviation = 1.8). The calculations were performed considering an *α* = 0.05, a statistical power of 80% and a follow-up loss of 15%. Thus, this study will comprise a sample of 222 patients who will be divided into three treatment groups (*n* = 74 patients per group).

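### The 1-month effect is read as a difference in change from baseline, which is valid but generally less precise than a baseline-adjusted contrast that the same data would give

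*Protocol article*

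**What the plan says.** The Statistical analysis section names linear mixed models for the primary analysis and fixes how the effect is read: "The differences between groups will be calculated by interaction terms of groups versus time". It then states "The time will be coded as a categorical variable (baseline, 1 month, 6 months and 12 months after randomization", so the baseline score is an outcome in the model. The section mentions neither a baseline covariate nor a constraint on baseline means. The Assessments section makes pain and specific disability at 1 month the primary outcomes.

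The Sample size calculation section plans "to detect a difference of 1 point on the Pain Numerical Rating Scale (estimated standard deviation = 1.84", and "1 point on the Patient-specific Functional Scale" with "estimated standard deviation = 1.8". It uses alpha 0.05, 80% power and 15% loss, and arrives at 74 per arm and 222 in total. It does not say whether the SDs belong to a score at one time or to a change, and it gives no correlation between baseline and follow-up.

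On timing, Table 1 puts the baseline measures before randomisation, whereas the Assessments section puts randomisation before the initial evaluation. The Procedures section says that neither patients nor therapist can be blinded.

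**The concern.** A difference in change subtracts the whole baseline score from the follow-up score, whatever the correlation between them. When the correlation is modest, this adds the noise of the baseline measurement to the contrast. A baseline-adjusted contrast subtracts only the part of baseline that predicts follow-up. With equal SDs at the two times and a correlation below 0.5, the difference in change is even less precise than comparing the 1-month scores and ignoring baseline.

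Precision is at stake for the primary contrasts. It matters most for the alliance group against usual treatment, where both arms receive the same information and the difference may be small. Because the sample size section gives no SD type and no correlation, nothing shows that the contrast to be tested has the SD used for planning.

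**Working it through.** **1. The plan's own figure.** Inputs from the Sample size calculation section: difference 1, SD 1.84 (pain) or 1.8 (function), alpha 0.05 (taken as two-sided), power 80%, loss 15%. The formula is n = 2(1.960 + 0.842)² SD² / 1².
- Pain: 53.1, so 54 per arm; 54/0.85 = 63.5, so 64 per arm and 192 in total.
- Function: 50.9, so 51 per arm; 51/0.85 = 60 per arm and 180 in total.

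The stated 222 is not reproduced, but it is larger and so errs on the safe side. Expected completers are 74 × 0.85 = 62.9, about 63 per arm.

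**2. What the interaction estimates.** With group, time and group × time in the model, the 1-month term is (arm A at 1 month − arm A at baseline) − (arm B at 1 month − arm B at baseline).

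**3. Variances per patient.** Let s0 and s1 be the SDs at baseline and 1 month, and rho their correlation.
- Change: s0² + s1² − 2·rho·s0·s1
- Baseline-adjusted: s1²(1 − rho²)
- With s0 = s1 the ratio is 2(1 − rho)/(1 − rho²) = 2/(1 + rho).

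**4. Power for pain if 1.84 is the SD of a single score.** Assumptions: equal SDs, 63 per arm, two-sided 5%, difference 1, noncentral t. At rho 0.3, for example, the change SD is 1.84 × √1.4 = 2.177 with SE 2.177 × √(2/63) = 0.388. The adjusted SD is 1.84 × √0.91 = 1.755 with SE 0.313.

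| rho | variance ratio | SD, change | power, change | SD, adjusted | power, adjusted |
|---|---|---|---|---|---|
| 0.2 | 1.67 | 2.327 | 67% | 1.803 | 87% |
| 0.3 | 1.54 | 2.177 | 73% | 1.755 | 89% |
| 0.4 | 1.43 | 2.016 | 79% | 1.686 | 91% |
| 0.5 | 1.33 | 1.840 | 86% | 1.593 | 94% |
| 0.6 | 1.25 | 1.646 | 92% | 1.472 | 97% |

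A plain 1-month comparison, ignoring baseline, has 86%. Change-score power is below 80% only for rho under about 0.41 for pain and about 0.38 for function (normal approximation; the t calculation moves each up by about 0.01).

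**5. The same in a four-time mixed model.** The model also uses the baselines of patients lost later (74 baselines, 63 follow-ups per arm; compound symmetry assumed). Interaction power becomes 75%, 81% and 87% at rho 0.3, 0.4 and 0.5, against 89%, 91% and 94% with equal baseline means. The 80% threshold moves to about 0.39.

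**6. If 1.84 is already the SD of change.** Interaction power is 86% for every rho. With equal SDs, adjustment multiplies the variance by (1 + rho)/2. At rho 0.7 the SD is 1.84 × √0.85 = 1.696 and power is 91%. At rho 0.3 it is 1.84 × √0.65 = 1.483 and power is 96%.

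**7. If the baseline SD is smaller than the follow-up SD.** For illustration, assume s0 = 1.3 and s1 = 1.84.
- rho 0.3: variances 3.640 and 3.081, ratio 1.18, power 83% against 89%.
- rho 0.4: variances 3.162 and 2.844, ratio 1.11, power 88% against 91%.

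The ratio reaches 1 when s0 = rho × s1.

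**The case against.** The strongest reply is that the planned analysis is valid and common, and that the article does not spell out every model term. It never mentions a group main effect. A model with equal baseline means also has baseline as a time level and also reads effects from interactions, so the wording does not exclude it. That stands as far as it goes. However, the text as written points to the usual full model, and nothing in it tells the analyst to do otherwise.

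Four stronger readings are tempting, and the documents do not support them.
- **The trial is underpowered.** This needs 1.84 to be a single-time SD, roughly equal SDs at both times, and a correlation under about 0.4. The article states none of these, and enrolling 74 rather than 64 per arm gives a margin.
- **The low-risk sample must have a low correlation.** A narrow baseline range could lower rho, but it also means a smaller baseline SD, which shrinks the penalty (step 7).
- **A fixed share of the sample is wasted.** The equal-SD ratio corresponds to 25% at rho 0.5 and 35% at rho 0.3. With unequal SDs the loss is smaller and can vanish.
- **The estimate is biased.** Under randomisation it is not. A chance baseline difference does carry into a change score in the realised trial, but that is a matter of precision.

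**Conclusion.** The point holds as a recommendation on efficiency, not as an error that invalidates the analysis. In the usual model, the planned 1-month effect is a difference in change, and a baseline-adjusted contrast is never less precise at the level of these variance formulas. The size of the gain depends on the correlation and on the two SDs, which the article does not give. On the single-time, equal-SD assumption the gain for pain is 16 percentage points of power at rho 0.3 (73% to 89%) and 8 at rho 0.5 (86% to 94%). If the planning SD is already that of change, power stays above the planned 80% and the gain is about 5 to 10 points (86% to 91–96%).

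**What to change.** Keep the linear mixed model and specify one of two forms before the data are unblinded:
- model the 1-, 6- and 12-month scores, with the baseline score and baseline × time as covariates; or
- keep all four times but constrain baseline means to be equal across arms: time plus group × post-baseline time, without a group main effect.

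Name the adjusted between-group difference at 1 month as the primary effect. State in the sample size section whether 1.84 and 1.8 are SDs of a score or of a change.

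First reconcile the Assessments section with Table 1 on whether baseline is measured before or after randomisation. Both forms require a baseline that allocation cannot have affected, and patients here are not blinded. Once that is settled, the cost is one line of model syntax, with no extra patients, visits or data.
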